### 2.7. Adverse Events

The present study confers a minimal risk of adverse events (AE). The safety (lack of AEs) of acute dosing of 300 mg DehydraTECH2.0 CBD has been established; and previous studies have used much higher acute dosing without reports of related AEs [4]. Specifically, the final daily dose (450 mg, approx. equally to 4.5 mg/kg/day) is 2–4-fold less than the reported 1500 mg/kg/day of CBD (or 10–20 mg/kg/day) used in the recent Phase 1 trial by Watkins et al. that revealed peak serum alanine aminotransferase values were above the upper limit of normal in 7 (44%) out of the 16 participants and exceeded international criteria for drug-induced liver injury in 5 (31%) of these participants [25]. In the aforementioned study, the most common all-causality AEs by preferred term were gastrointestinal disorders, including diarrhea in eight (50%) participants and abdominal discomfort in five (31%) participants. Most of these AEs were first experienced during the CBD titration phase. All reported AEs were either mild (31%) or moderate (50%) in severity. Of note, CBD is a commercially available dietary supplement. Nevertheless, we will monitor both AEs and serious AEs (SAEs). Subjects are instructed to contact a study team member if any AE occurs and permission to reach out to emergency contacts has been requested from all participants in case of the subjects not being responsive. The principal investigator of the study, alongside two study investigators holding a medical degree, will continuously monitor the conduct, data, and safety of the study, including monitoring and tabulating AEs. Potential AEs will be evaluated in accordance with the Common Terminology Criteria for Adverse Events (CTCAE) V.5.0 and AEs will be graded based on the likelihood of being related to the study intervention [26]. MedDRA PT (version 24.1) will be used for documenting any AE and serious AEs. All SAEs will be reported to the local Institutional Review Board (IRB) according to good clinical practices within 24 h for potentially life-threatening events and within 5 business days for non-life-threatening events. If such event occurs, the participant will immediately stop receiving treatment and be excluded from study. Additionally, an internal safety monitor will adjudicate all SAEs for report completeness, seriousness of event, and relationship to study interventions. The trial will terminate immediately if 20% of involved participants report SAEs.

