## 2. Materials and Methods

### 2.1. Study Design and Setting

The present single-center study is designed as a triple blind (Participant, Investigator, Outcomes Assessor), placebo-controlled, crossover pilot study in which 70 hypertensive volunteers (aged 40–70 years) will receive DehydraTECH2.0 CBD formulation and placebo in a cross-over manner. The study protocol was registered at the ClinicalTrials.gov (accessed on 7 April 2022) (NCT05346562). The sequence of conditions the participant will receive will be generated by a research randomizer web-service (https://www.randomizer.org, accessed on 7 April 2022) and participants will complete: (1) placebo-control and (2) DehydraTECH^TM^ CBD (225 to 300 mg split over three times daily for the initial 2.5 weeks and 375 to 450 mg split over three times for the following 2.5 weeks). Following a two-week washout, participants will then repeat testing for another five weeks under different conditions. Participants will visit the laboratory on 6 occasions in total (3 in each study arm), each time following an overnight fast. The complete course of the study will be performed at the Department for Integrative Physiology, University of Split School of Medicine, Split, Croatia. The study design, implementation, and reporting will follow the CONSORT guidelines, including the 25-item checklist and a flow diagram (Figure 1). The study will be conducted according to the guidelines of the Declaration of Helsinki and was approved by the Ethics Committee of University of Split School of Medicine on 15 December 2021 (Class: 003-08/21-03/0003; Reg. No.: 2181-198-03-04-21-0091). Prior to enrollment in the study, every participant was informed about the procedures, course, and purpose of the research and each of them individually signed an informed written consent. 

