#### 2.2.2. Exclusion Criteria

Current smoker or using vapor-based products; or a medical or recreational cannabis userSecondary hypertensionActive malignant diseaseGoutHistory of psychosis and/or depression and/or clinically diagnosed anxietyChronic kidney diseaseChronic gastrointestinal disease (e.g., irritable bowel syndrome, celiac disease, inflammatory bowel disease, chronic diarrhea) or has had a cholecystectomy in the pastCurrent diagnosis or history of any seizure disorderHeart failureDiabetes mellitusPregnant, breast feeding, or plan to become pregnantHistory of opioid useDual blood pressure therapy other than ACE inhibitors with diuretic or ACE inhibitors with Calcium Channel blocker with or without diuretics (e.g., ACE inhibitors with beta blockers)Unwilling or unable to execute the informed consent documentationLiver disease, including taking valproate, confirmed on baseline blood biochemistry—exclusion of subjects that have >1.5 upper limit of normal (ULN) for alanine transaminase (ALT) or aspartate transaminase (AST), total bilirubin (TBL) > ULN at baseline determined by local reference population values in Croatia:
oULN for ALT 48 IU/LoULN for AST 38 IU/LoULN for TBL 20 μmol/L

The above noted inclusion/exclusion criteria are assessed with a medical screening questionnaire during a clinical examination and related baseline blood chemistry. If at any point during the trial participants meet any of the following criteria, they will be excluded:ALT or AST > 3x ULN accompanied by fever, rash, fatigue, nausea, vomiting, right upper quadrant pain or tenderness, and/or eosinophilia (>5%)ALT or AST > 5x ULNALT or AST > 3x ULN and TBL > 2x baseline

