### 2.5. Laboratory Visits

The initial screening visit was comprised of initial assessment of anthropometrics (height, weight, waist and neck circumference), blood pressure and relevant vital signs, assessment of eligibility for study participation, and obtaining the past medical history. A total of 117 volunteers were screened, 15 patients did not meet the inclusion criteria and 30 patients met the exclusion criteria. After the completion of the screening procedures, eligible participants were randomly assigned to one of the two experimental groups. Following randomization, participants will undergo their first set of physiological, neuroimaging, sleep, and cognitive assessments. Additionally, participants will complete several lifestyle and psychological questionnaires (Table 2). This battery of assessments will be completed again following 2.5 weeks and after 5 weeks, and then repeated immediately after the washout period, 2.5 weeks after that, and 5 weeks after finishing the washout period. There will be 6 experimental visits in total to the laboratory, with additional 4 visits to the MRI suite (in selected subjects that will undergo neuroimaging). Participants will report to the laboratory after an overnight fast (>10 h) and around 07:30. Of note, subjects will be reminded to not perform exercise or to consume alcohol 24 h prior to the next visit. Water intake will be measured and allowed *ad lib*. During each experimental visit, a sample of venous blood will be taken from the forearm (cubital vein) using a sterile disposable needle and a previously cleansed skin surface. All blood samples will be procured in the early morning visit, prior to consuming the CBD or placebo capsules. This procedure will be performed by a trained laboratory technician. A maximum of 3 to 22 mL of blood will be drawn. Part of the sampled blood will be sent for immediate analysis, whereas part of the sample will be aliquoted and stored on −80 °C for subsequent analysis of biomarkers. All blood samples will be analyzed in the same certified institutional biochemical laboratory, by using the standard operating procedures. In addition, a sample of urine will be collected and stored for analysis of CBD and its metabolites with LCMS in plasma and urine.

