Following the extraction of the initial blood sample, subjects will be evaluated using bioelectrical impedance scale Tanita DC-360 S (Tanita, Tokyo, Japan) and AGE Reader and then instrumented with the 24-h ambulatory blood pressure monitor that will be used to assess continuous blood pressure measurements away from the laboratory. The device will be set to take measurements every 30 min through the day (08:30–23:00) and every hour through the night (23:00–8:00). Subjects will be also instrumented with 24-h ECG monitor. Subjects will also be asked to wear a Fitbit activity and sleep monitor. Finally, prior to discharge, subjects will be given an appropriate set of questionnaires. Apart from the bioelectrical impedance analysis which will be performed only during experimental visit 1 and 4, and AGE Reader measurement, which will be performed during visits 1, 3, 4, and 6, the protocol will be the same for all experimental visits. The whole procedure will take about 40 min per visit.

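### The SAE rule, and on its natural reading the in-trial liver rule, removes the participant from the study as well as from the capsules, so the remaining scheduled liver tests are given up

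*Protocol article*

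**What the plan says.** Two rules in the protocol article remove participants during the trial.

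- **SAE rule (Section 2.7).** After giving reporting times for both life-threatening and other SAEs, the article says that if such an event occurs "the participant will immediately stop receiving treatment and be excluded from study". It sets no condition on relatedness. The same section adds that "an internal safety monitor will adjudicate all SAEs for report completeness, seriousness of event, and relationship to study interventions".
- **Liver rule (Section 2.2.2).** "If at any point during the trial participants meet any of the following criteria, they will be excluded". Three criteria follow: ALT or AST above 3 times ULN with symptoms or eosinophilia; ALT or AST above 5 times ULN; and ALT or AST above 3 times ULN with bilirubin above twice baseline.

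On the schedule, Section 2.5 says "There will be 6 experimental visits in total to the laboratory", and Table 2 places liver transaminases at screening and at all six visits. Section 1 names the safety and tolerability of five weeks of CBD as a secondary aim. Section 2.4 measures safety by blood biomarkers and tolerability by adverse event reports.

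**The concern.** The SAE rule orders two acts: stopping treatment and leaving the study. The first protects the participant. The second adds no protection, and it ends the visits at which recovery would be seen. The participants who trigger a liver rule are those whose values after stopping say most about whether the change reverses. Adjudicating an SAE report documents the event, but it is not a repeat liver test. Section 2.9 leaves the handling of missing data to a later analysis plan, and no analysis can recover a sample that was never drawn. What is at stake is safety information for a named secondary aim.

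**Working it through.** The article gives no figure for this loss, so there is none to reproduce. The check counts what the schedule holds after each possible trigger.

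**Inputs.** Each period has visits at weeks 0, 2.5 and 5 (Table 2). On the gap between periods, Section 2.1 says: "Following a two-week washout, participants will then repeat testing for another five weeks under different conditions". Transaminases are tested at all six visits (Table 2). The participant number used is 72 (Section 2.6; Section 2.1 says 70, which changes nothing material here).

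**Visit weeks.** V1 = 0, V2 = 2.5, V3 = 5, V4 = 5 + 2 = 7, V5 = 7 + 2.5 = 9.5, V6 = 7 + 5 = 12.

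**Liver trigger on CBD.** Tests given up = 6 − visit number. Time since stopping = later visit week − trigger week, taking capsules to stop at the trigger visit.

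| Trigger | Sequence | Tests given up | Weeks after stopping |
|---|---|---|---|
| V2 | CBD first | 6 − 2 = 4 | 2.5, 4.5, 7, 9.5 |
| V3 | CBD first | 6 − 3 = 3 | 2, 4.5, 7 |
| V5 | Placebo first | 6 − 5 = 1 | 2.5 |
| V6 | Placebo first | 6 − 6 = 0 | none |

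Except at V6, a test 2 to 2.5 weeks after stopping is already scheduled and is given up.

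**SAE.** The loss depends on when the SAE occurs, not on the capsule taken: 5 visits before V2, 4 between V2 and V3, 3 in washout, 2 between V4 and V5, and 1 between V5 and V6.

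**Illustrative size.** No document gives a trigger rate at these doses. Assume that 1% to 10% of 72 participants have a liver trigger on CBD.

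- Scheduled on-study tests: 72 × 6 = 432.
- Mean loss per trigger, split evenly over sequences and visits: ((4 + 3)/2 + (1 + 0)/2)/2 = 2.0 tests.
- At 1%: 0.72 participants, 1.44 tests, 1.44/432 = 0.3%.
- At 5%: 3.6 participants, 7.2 tests, 7.2/432 = 1.7%.
- At 10%: 7.2 participants, 14.4 tests, 14.4/432 = 3.3%.
- If triggers occurred only after the higher dose step (V3 and V6), the mean loss is (3 + 0)/2 = 1.5 tests. The range is then 1.08 to 10.8 tests, or 0.25% to 2.5%.

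**The case against.** Several objections carry weight.

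- **The loss of tests is inferred.** The article nowhere says that later tests are not taken, and a fuller protocol could provide safety follow-up after withdrawal. This stands as a limit on certainty. It does not remove the point, because the article states a rule whose plain effect is to end participation, and nothing in the article contradicts that effect.
- **Scheduled adverse event assessments.** A reader might infer that these are lost too. Table 2 has no such row. Under Section 2.7, adverse events come from participants contacting the team and from continuous monitoring by the investigators. What would stop is that monitoring.
- **The liver rule does not say what the participant is excluded from.** This is so. Its position directly after the study eligibility criteria makes the study the natural reading, but only the SAE rule is explicit. A non-hepatic SAE also gives less reason for later liver tests than a liver trigger does.
- **The size is small and assumed.** Both the rate and the even split are assumptions. Triggers may cluster after the higher dose, and Table 2 places the wider blood biomarkers, which include bilirubin, only at weeks 0 and 5. The loss is a few percent of tests at most under the range shown.
- **The remaining visits are not a recovery protocol.** They follow a fixed calendar and do not require testing until values resolve. This too stands.

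**Conclusion.** The point holds as a cheap improvement of low severity. After any SAE the article removes the participant from the study, and the liver rule most naturally does the same. Followed as written, up to 4 scheduled off-capsule liver tests are given up after a liver trigger on CBD, and up to 5 visits after an early SAE.

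The number of participants affected is unknown and probably small. The liver signal that Section 2.7 cites comes from a dose which the article puts at 2 to 4 times the trial's highest.

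Two stronger readings are not supported:

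- A reader might infer that the triggering event goes unrecorded or that earlier data are discarded. Section 2.7 provides for recording adverse events and for reporting and adjudicating SAEs, and nothing in the article says that earlier data are deleted.
- A reader might infer a material bias in the 24-h blood pressure comparison. The missing treatment period results from stopping the capsules, which is right on safety grounds, and the few people involved make any effect minor.

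**What to change.** In Sections 2.2.2 and 2.7, replace exclusion with wording such as: *permanently discontinued from study capsules, but retained, with the participant's agreement, for the remaining scheduled visits for liver tests and adverse event follow-up*. Keep every stopping threshold and all data observed before discontinuation. Flag any later blood pressure as off-treatment, not as CBD or placebo data.

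**Cost.** No new visits are needed. On visit length, Section 2.5 says "The whole procedure will take about 40 min per visit". The burden is therefore at most about 4 × 40 = 160 minutes after a liver trigger at a scheduled visit, or 5 × 40 = 200 minutes after an early SAE. If a participant also agrees to 24-h blood pressure and ECG recording, that adds at most 4 × 24 = 96 or 5 × 24 = 120 hours of monitor wear.

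**Limits.** Off-treatment blood pressure adds little to the crossover contrast, and the lost treatment period is not restored. The change does not help a trigger at V6. A repeat test there, or testing until values resolve, would be an added procedure for the sponsor to weigh separately.

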### 2.8. Data Collection and Management

Obtained data of interest will be recorded during each visit and entered on a special research form (respondents’ card) by study researchers, and it will subsequently be archived and protected by a unique code of the participant. For keeping data, we will use a paired digital archive consisting of computer’s internal memory and external hard drive. The lab book will be kept at the Department of Integrative Physiology, and after the research is completed, the raw data will be available on request from the corresponding author. The data will not be publicly available because some of the dataset will be used for further research.

### 2.9. Statistical Analysis Plan

Collected data will be analyzed with the statistical software SPSS statistics (version 21.0, IBM, Chicago, IL, USA) and Prism 6 for Windows^®^ (version 6.01, GraphPad, La Jolla, CA, USA). Quantitative data will be expressed as mean ± standard deviation or median and interquartile range, as appropriate, while qualitative data will be expressed as a whole number and percentage. Kolmogorov–Smirnov test will be used to estimate the normality of data distribution. A comparison of quantitative variables will be conducted using Student’s *t*-test for independent samples, or Mann–Whitney U tests where appropriate. Data will be analyzed for repeated measures analysis using either general or mixed linear models (with sex, body mass, medication, and age as a co-variates). Yet, the final analysis plan, which includes analyses of the secondary outcomes and strategies for handling missing/incomplete data, will be formalized by the biostatistician prior to breaking the blind. The data analysis will only begin once data collection is complete. Significance will be set at *p* < 0.05 for all comparisons.

## 3. Rationale for Conducting the Trial

Accumulating data from both human and animal studies suggests that CBD may be associated with improved cardiovascular function, markedly with regards to reduction in blood pressure and improved endothelial function [27,28,29]. Nevertheless, there is a lack of randomized studies to support these notions, especially in at-risk populations. Therefore, in the present trial, the primary endpoint will be reduction in 24-h ambulatory blood pressure. Specifically, we will assess its effects on both treated and treatment-naïve patients with essential hypertension. In order to further elucidate and quantify the effects of CBD, we will explore its effects on arterial stiffness, serum levels of endothelial dysfunction biomarkers, and autonomic nervous system modulation on the cardiac sinus node. In addition, using the panel of validated questionnaires, the psychological well-being will be determined in both groups of patients. We believe that comprehensive analyses that will be performed in the present trial will decipher whether CBD is in fact a safe and valuable supplement for patients with treated and untreated hypertension. In addition, understanding new approaches to CBD delivery has major implications for more precise recommendations of CBD usage in health and disease states.

## Figures and Tables

**Figure 1 jpm-12-01037-f001:**
[figure not shown]
CONSORT flow diagram.

**Table 1 jpm-12-01037-t001:** Dosing schedule.

Randomization Group	Dose Period 1 (2.5 Weeks)	Dose Period 2 (2.5 Weeks)
DehydraTECH2.0 CBD	** *≤75 kg: CBD, 225 mg/day* **	** *<100 kg: CBD, 375 mg/day* **
	75 mg morning (1 capsule)	75 mg morning (1 capsule)
	75 mg afternoon (1 capsule)	150 mg afternoon (2 capsules)
	75 mg bedtime (1 capsule)	150 mg bedtime (2 capsules)
	** *>75 kg: CBD, 300 mg/day* **	** *≥100 kg: CBD, 450 mg/day* **
	75 mg morning (1 capsule)	150 mg morning (2 capsules)
	75 mg afternoon (1 capsule)	150 mg afternoon (2 capsules)
	150 mg bedtime (2 capsules)	150 mg bedtime (2 capsules)
Placebo	Placebo, number of capsules matched to active treatment based on body weight	Placebo, number of capsules matched to active treatment based on body weight

Abbreviations: CBD: cannabidiol.

**Table 2 jpm-12-01037-t002:** Schedule of measurements.

Assessment Measure	Screening	First Set of Visits			Washout	Second Set of Visits		
Timing of visit (weeks)		0	2.5	5		0	2.5	5
**Anthropometry and medical history**								
Medical history	✓							
Demographics and health history	✓							
Eligibility screening questionnaire	✓							
Anthropometrics and vital signs	✓	✓	✓	✓		✓	✓	✓
Bioelectrical impedance analysis		✓				✓		
**Indices of cardiovascular health**								
24-h ambulatory blood pressure		✓	✓	✓		✓	✓	✓
24-h ambulatory ECG		✓	✓	✓		✓	✓	✓
Pulse wave analysis		✓	✓	✓		✓	✓	✓
AGE Reader		✓						
Brain structure and function (MRI)		✓		✓		✓		✓
**Blood work and urine analysis**								
Blood biomarkers		✓		✓		✓		✓
Liver transaminases	✓	✓	✓	✓		✓	✓	✓
Cannabidiol in urine		✓	✓	✓		✓	✓	✓

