### 2.3. Study Arms and Interventions 

Participants allocated in the first arm (Cannabidiol, then Placebo) will first receive cannabidiol: 225 to 300 mg (depending on the sex and weight of the participants) split over three times daily for the initial 2.5 weeks and 375 to 450 mg split over three times for the following 2.5 weeks. After two-week washout, participants will receive Cannabidiol-matched placebo tablets for five weeks. Participants allocated in the second arm (Placebo, then Cannabidiol) will receive Cannabidiol-matched placebo tablets for five weeks. After two-week washout, participants will receive cannabidiol: 225 to 300 mg split over three times daily for the initial 2.5 weeks and 375 to 450 mg split over three times for the following 2.5 weeks. A detailed dosing regime is presented in Table 1. The production of both placebo and capsules containing CBD was done in accordance with the standard operating procedures by experienced chemical engineers. The manufacturing process was performed using the services of a Good Manufacturing Practices (GMP)-compliant contract manufacturer located in the United States. The DehydraTECH2.0 CBD formulation was comprised of Lexaria Bioscience Corp.’s patented mixture of long chain fatty acid rich triglyceride oil and tetrahydrocannabinol-free, purified cannabidiol distillate oil, together with organic substrate powder ingredients and other organic constituents included to enhance intestinal absorption performance. The DehydraTECH2.0 CBD formulation was prepared as a powder and filled into Size 00 vegan gel capsules at a target strength per capsule of 75 mg CBD as independently verified via high-performance liquid chromatography (HPLC) upon quality control testing. The DehydraTECH2.0 CBD formulation used in the present study was also subjected to Lexaria Bioscience Corp.’s patented performance-enhancing dehydration processing methodology. The placebo capsules were simply filled with an organic substrate powder ingredient devoid of any CBD active drug substance as also verified upon HPLC testing, and similarly filled into matching Size 00 vegan gel capsules for blinding purposes. 

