The secondary outcomes are: Cannabidiol levels in peripheral blood sample.Safety (via blood biomarkers, #8 and tolerability (via adverse event reporting).Calories burned, total sleep time, number of awakenings—Physical activity and sleep quality (actigraphy) will be monitored via a wrist-based health and fitness tracker FitBit (Fitbit Inc., San Francisco, CA, USA) with a large organic light-emitting diode screen featuring heartrate monitoring and tracking of steps, distance, calories burned, floors climbed, active minutes, and sleep duration. These devices have been well-validated against gold-standard measures with good accuracy [11].Pulse wave velocity, augmentation index, and total peripheral resistance measured by Schiller BR-102 plus PWA (Schiller AG, Baar, Switzerland).Volume of hippocampus and internal carotid artery blood flow—Volume of hippocampus will be assessed by magnetic resonance imaging (MRI), T1-MPRAGE sequence, whereas blood flow through internal carotid artery will be measured by 1.5T MRI, 4D flow.Heart rate variability measured by Schiller medilog^®^AR Holter recorder (Schiller AG, Baar, Switzerland).Cardiovascular risk assessed by tissue levels of advanced glycation end-products (AGEs)—The AGE Reader (DiagnOptics Technologies BV, Groningen, The Netherlands) is a non-invasive monitoring device that uses ultra-violet light to excite autofluorescence in human skin tissue. The autofluorescence reflects tissue levels of AGEs [12]. The measurement of AGEs provides an immediate cardiovascular risk prediction in 12 s. The AGE Reader has been designed for patient-friendly diagnosis; the method is convenient, easy to use, and extensively validated.Circulating levels of blood biomarkers—Circulating (steady-state) plasma concentrations of CBD, inflammation (including TNF-alpha, IL-6, IL-10, whole blood count, etc.) and gold-standard biomarkers of plasma nitric oxide (plasma nitrite, s-nitrosothiols, and total nitric oxide) will be measured from peripheral blood sample. Lipids (cholesterol, high- and low-density lipoprotein, and triglycerides), glucose, insulin, HbA1C, renal (creatinine), hepatic (ALT, AST, ALP, GGT, and total bilirubin), drug toxicity (acyl glucuronide), and cardiovascular disease markers (hs-CRP) will also be measured.Outcomes assessed using questionnaires:

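### Table 2 conflicts with sections 2.2.2 and 2.5 at the two week-2.5 visits: it ticks transaminases but not the row that appears to hold total bilirubin and blood count

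*Protocol article*

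**What the plan says.** **Withdrawal rules (section 2.2.2).** The liver triggers are introduced with "If at any point during the trial participants meet any of the following criteria, they will be excluded". There are three:

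1. ALT or AST above 3 × ULN with any of several symptoms or signs; that list closes with the words "and/or eosinophilia (>5" (the figure is a percentage).
2. ALT or AST above 5 × ULN.
3. ALT or AST above 3 × ULN together with TBL above twice baseline.

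The stated ULNs are 48 IU/L for ALT, 38 IU/L for AST and 20 μmol/L for TBL. For entry, liver disease is to be "confirmed on baseline blood biochemistry", with TBL above the ULN excluded.

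**Where the tests sit (section 2.4).** The item on circulating blood biomarkers includes both "hepatic (ALT, AST, ALP, GGT, and total bilirubin" and "inflammation (including TNF-alpha, IL-6, IL-10, whole blood count, etc".

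**Schedule (Table 2).** The row "Liver transaminases" is ticked at screening and at all six experimental visits. The blood-biomarker row is ticked at weeks 0 and 5 of each period, and is blank at screening and at both week-2.5 visits.

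**Visit text (section 2.5).** It states "This battery of assessments will be completed again following 2.5 weeks and after 5 weeks". It has venous blood taken at every experimental visit, with part of it analysed at once. It describes the visits as identical except for bioimpedance and the AGE Reader.

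**Dosing (section 2.3 and Table 1).** After the first 2.5 weeks on CBD, the daily dose becomes "375 to 450 mg split over three times for the following 2.5 weeks".

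**The concern.** A withdrawal rule works only if the values it uses are available when a decision can still be made. Each dosing course lasts five weeks and has one scheduled visit inside it, at week 2.5. Week 0 precedes the course and week 5 closes it, so week 2.5 is the one planned visit at which withdrawal would shorten exposure. It is also where the CBD dose is raised.

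A site that follows Table 2 row by row would have ALT and AST at that visit, but neither TBL nor an eosinophil count. A participant who meets the TBL trigger, or the first trigger through eosinophilia alone, could then go on to the higher dose until the week-5 sample. The protocol treats liver injury as a real risk. Section 2.7 cites a phase 1 trial, at a dose it describes as 2 to 4 times higher, in which 5 of 16 participants exceeded drug-induced liver injury criteria. That figure does not estimate how often this would happen at the present dose.

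**Working it through.** No sample-size, power or alpha figure bears on this point. The check sets Table 2 against the triggers and then sizes the gap.

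**Step 1. Ticks by visit (Table 2).**

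| Row | Screening | Wk 0 | Wk 2.5 | Wk 5 | Wk 0 | Wk 2.5 | Wk 5 |
|---|---|---|---|---|---|---|---|
| Transaminases | yes | yes | yes | yes | yes | yes | yes |
| Blood biomarkers | no | yes | no | yes | yes | no | yes |

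Transaminases are tabled at 6 of 6 experimental visits and blood biomarkers at 4 of 6. The two missing are exactly the two week-2.5 visits.

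**Step 2. Thresholds (ULNs from section 2.2.2).**
- 3 × ULN: ALT 3 × 48 = 144 IU/L; AST 3 × 38 = 114 IU/L.
- 5 × ULN: ALT 5 × 48 = 240 IU/L; AST 5 × 38 = 190 IU/L.

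**Step 3. Can each trigger be evaluated from the tests tabled at week 2.5?**
- Above 5 × ULN: yes, it needs transaminases only.
- Above 3 × ULN with symptoms and/or eosinophilia: yes through any listed symptom; no if eosinophilia is the only accompanying sign.
- Above 3 × ULN with TBL above twice baseline: no.

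One of the three triggers is fully blocked and one loses a single branch. The affected participant has none of the listed symptoms, at least one enzyme above 3 × ULN (ALT above 144 or AST above 114 IU/L), neither above 5 × ULN (ALT at most 240, AST at most 190 IU/L), and either TBL above twice baseline or eosinophils above 5%.

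**Step 4. Does the TBL trigger need a laboratory value?** The trigger is 2 × baseline. Individual baselines are not given, so these are assumed values up to the entry maximum:
- baseline 5: above 10 μmol/L
- baseline 10: above 20 μmol/L, which is the ULN
- baseline 20: above 40 μmol/L

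For any baseline below 10 μmol/L the trigger lies inside the reference range, so only an assay can show it.

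**Step 5. Delay and exposure.** From week 2.5 to the next tabled TBL at week 5 is 2.5 × 7 = 17.5 days.
- At 375 mg/day (below 100 kg): 17.5 × 375 = 6,562.5 mg, about 6.6 g.
- At 450 mg/day (100 kg or more): 17.5 × 450 = 7,875 mg, about 7.9 g. With BMI below 30 kg/m² this dose applies only to participants taller than √(100/30) ≈ 1.83 m, so 6.6 g is the usual figure.

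This exposure arises in the CBD course only, at one of each participant's two week-2.5 visits.

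**Step 6. Table against text.** Section 2.5 names bioimpedance and the AGE Reader as the only differences between visits; blood tests are not excepted. Table 2 makes them differ. The table also disagrees with section 2.5 on the AGE Reader: visits 1, 3, 4 and 6 in the text, one tick in the table.

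**The case against.** The strongest reply is that Table 2 does not define its rows. The hepatic list in section 2.4 that contains TBL also contains ALT and AST, which have their own row, so the rows do not map one-to-one onto section 2.4. TBL is an entry criterion, section 2.5 randomizes after screening, and the transaminase row is the only blood row ticked at screening. The simplest reading may be that this label stands for a liver panel including TBL, in which case TBL is covered at week 2.5 as well. This stands as a real possibility. It would call for a clearer label, and it would not supply an eosinophil count.

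Second, section 2.5 draws blood at every visit and implies the same work-up. That also stands, although its wording is general: the statement that the battery is repeated cannot hold for MRI, which has four visits. A reader might infer from Table 2 that TBL and blood count are never measured at week 2.5. The documents do not support that; they show only that table and text disagree.

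Third, an any-time rule does not promise every component test at every visit. Every affected case would first show a scheduled ALT or AST above 3 × ULN, to investigators who monitor safety continuously under section 2.7, and follow-up of an abnormal result is detail that an article may leave to the full protocol. This narrows the consequence considerably. It does not remove the disagreement between a printed schedule and printed text.

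**Conclusion.** The point holds as a conflict between Table 2 and sections 2.2.2 and 2.5 at both week-2.5 visits. Read literally, the table leaves the TBL trigger without its bilirubin value and removes the isolated-eosinophilia branch of another trigger, for up to 17.5 days at the higher dose.

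A reader might infer that two whole triggers are inoperable. They are not: the and/or wording keeps the symptom route of the first trigger open, and the 5 × ULN rule is untouched.

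The conclusion rests on one inference, that TBL and blood count belong to the blood-biomarker row because section 2.4 lists them there. The documents give no basis for estimating how often the affected case would occur. No efficacy endpoint, estimate or threshold is touched. Severity is minor.

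**What to change.** Correct Table 2 and leave every threshold unchanged.

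- Show TBL at both week-2.5 visits, run on the blood already drawn. If the transaminase row was meant as a liver panel, relabel it to say that it includes TBL.
- At minimum, require TBL and a differential count as reflex tests on the same sample whenever ALT exceeds 144 or AST exceeds 114 IU/L, with the results reviewed before the higher dose continues. The differential is needed even if the row is relabelled, because a liver panel contains no eosinophil count.
- Show TBL at screening, to match the entry criterion in section 2.2.2.

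Because the trial is blinded, the tests apply in both courses. Routine testing at week 2.5 costs at most 70 × 2 = 140 assays of each kind with the 70 participants of section 2.1, or 72 × 2 = 144 with the 72 of section 2.6. Reflex testing costs far fewer. No extra blood draw or visit is needed.
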